#### 3.3.2. Devices for Recording Physiological Data

During the sessions, we will use 4 wearable devices developed in the context of this project to collect data. Figure 1 shows a diagram of the sensors that will be used.

These are 4 devices that distribute sensors throughout the body, comprising 4 inertial units on the wrist, ankle, chest and head: a wrist temperature sensor; a sensor of the electrical activity of the skin (EDA) in the phalanges (using dry electrodes placed on the thenar and hypothenar eminences of the dominant hand); an electrocardiography sensor on the chest; and 16 channels of electroencephalography (EEG). In addition, the ambient temperature can be recorded.

One of the wearables we will use is the OpenBCI device (accessed on https://openbci.com/, accessed on 10 May 2024). It is a 16-channel bioamplifier for EEG measurement open-source and low-cost hardware that measures at a maximum rate of 125 Hz when 16 channels are used and includes an inertial unit that measures at 25 Hz. In Figure 2, the electrode position is indicated. The figure shows the positions of the electrodes included in the 10/20 system, which are FP1, FP2, F1, F2, F5, F6, Cz, C3, C4, T7, T8, Pz, P3, P4, O1 and O2. Additional reference and ground electrodes will be placed on the right ear and FPz positions, respectively. The system has been validated in various studies, and the electrode positions it utilizes allow for the measurement of all brain regions, providing sufficient information about the subject’s state.

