(3)$$pNN50=\frac{100}{N-1}\sum_{i=2}^{N}u(|RR_{i}-RR_{i-1}\left|-50ms\right)$$Skin conductance level (SCL) and skin conductance response (SCR) to detect slow and fast variations in EDA, respectively.Fractal dimension (FD) of EEG to compute its complexity using Higuchi’s algorithm.The spectrum entropy (SE) of EEG is a tool to determine the EEG complexity. The initial step involves acquiring the power spectral density (PSD). The PSD is then normalized by the number of bins, effectively converting it into a probability density function. Finally, the traditional Shannon entropy for information systems is computed.EEG coherence. The interplay among neural systems, functioning within each frequency band, is approximated through EEG coherence. The amplitude of EEG is affected by neural synchronization, while the coherence of signals obtained by a pair of electrodes indicates the uniformity and steadiness of the signal’s amplitude and phase. A time delay in the signal should be observable between two interconnected brain regions, which is interpreted as a phase shift in the frequency domain.

Regarding the possibility of muscle activity influencing EEG signal measurements, it is important to note that the muscles engaged in the activity are typically distant from the openBCI, and thus their influence is negligible. EEG is more likely to be affected by facial muscles, head movements, etc. For such cases, Independent Component Analysis (ICA) will be utilized, as it is an efficient algorithm for source separation and artifact removal in EEG signals. The data will be recorded in a synchronized manner using a software application (Figure 3) designed for this purpose [34]. The software utilizes the LabStreaming Layer library. This library supplements each captured data point with a timestamp generated by a high-resolution local clock, simplifying data synchronization. Additionally, the library employs the Network Time Protocol (NTP) to estimate communication delays, thereby adjusting the time offset between clocks.

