### 4.2. Data Analysis

In general, numerical variables will be expressed as mean (M) and standard deviation (SD), including range, minimum and maximum.

For the first part of the study, we will compare the dependent variables obtained between sessions 1 and 2 for each subject using the permutation test of the difference in means between different data windows. Those dependent physiological variables that mark significant differences for most of the subjects will be chosen. Changes in EVEA test responses between sessions 1 and 2 will serve as reinforcement for detecting the level of emotional change.

We will also correlate the results of the EVEA test with the base state questionnaires to determine the existence of some type of dependency between the base level of EVEA and its variation with respect to the base state. This dependence will be explored with the Spearman or Pearson correlation test.

For the second part, first, we will analyze the variation in EVEA for sessions 3 and 4 to determine if there is a significant dependence on the independent variable (music) between stages A and B for all the participants. We will use the Kruskal–Wallis test, which does not require any type of assumption regarding the normality and homoscedasticity of the samples. These variations will also be correlated with the quality of life scale (ICF, GMFCS, MACS, CFCS, or KIDSCREEN), as was carried out with the data from the first part.

For the physiological variables and the average kinetic energy, we will determine if their variations are significant between A and B by means of a Kruskal–Wallis test applied to the group of subjects, but also at the individual level by means of a permutation test.

The significance of the tests will be set at three levels, indicated with * (*p* < 0.05), ** (*p* < 0.01) and *** (*p* < 0.001).

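### EEG spectral entropy is normalised by the number of bins, which does not give a probability distribution, so the variable as defined mixes EEG power and units with spectral complexity

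*Protocol article*

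**What the plan says.** Section 3.3.2 of the protocol article introduces the variable by its purpose: "The spectrum entropy (SE) of EEG is a tool to determine the EEG complexity". It starts from the power spectral density (PSD) and then gives the normalising rule: "The PSD is then normalized by the number of bins, effectively converting it into a probability density function". The last step is "Finally, the traditional Shannon entropy for information systems is computed". No equation is given for SE, and no division by total power is mentioned. The EEG device "measures at a maximum rate of 125 Hz when 16 channels are used".

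Section 4.2 uses the physiological variables twice. In the first part, sessions 1 and 2 are compared within each subject by a permutation test over data windows, and "Those dependent physiological variables that mark significant differences for most of the subjects will be chosen". In the second part, for silence (A) against music (B), "we will determine if their variations are significant between A and B by means of a Kruskal–Wallis test applied to the group of subjects", with an individual-level permutation test as well.

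**The concern.** The number of bins is fixed by the segment length and sampling rate and carries no information about how much power the signal holds. Dividing by it rescales every PSD value by the same constant, so the result is still a PSD with physical units. Shannon entropy is defined for probabilities that sum to 1. Applied to anything else, it loses its bounds (0 to log2 of the number of bins) and its invariance to scale.

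This matters because SE is compared between sessions. Section 3.3.3 has the sensors placed at the start of each session, and the sessions involve different activities. Section 3.3.2 itself expects facial muscles and head movement to affect the EEG. A session-wide shift in recorded power would move all windows of that session together and could be read as a change in complexity. SE could then be selected in the first part and carried into the music comparison for a reason other than the one the article gives.

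**Working it through.** The article gives no numerical value for SE, so there is no figure to reproduce. What can be checked is the stated property: do the normalised values form a probability distribution?

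**Algebra (no assumptions).** Let P_k be the PSD in bin k of N.
- As written: q_k = P_k / N. Then sum(q) = sum(P) / N = c, the mean PSD. This equals 1 only by coincidence of units and power.
- Proper normalisation: p_k = P_k / sum(P), which sums to 1. Hence q_k = c·p_k.
- Substituting: −sum q_k log2 q_k = −sum c·p_k (log2 c + log2 p_k) = c·H(p) − c·log2(c).

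The as-written value is thus a function of two things: spectral shape, through H(p), and mean power, through c.

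**Illustration 1.** From the article: 125 Hz. Assumed: 126 bins of 0.5 Hz, one fixed 1/f-type spectrum with H(p) = 4.13 bits, RMS 5 to 40 microvolts. The PSD integrates to the variance, so sum(P) = variance / 0.5 and c = 2·RMS² / 126 = RMS² / 63.

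| RMS (microvolts) | c | c·(4.13 − log2 c) | Direct simulation | Proper SE |
|---|---|---|---|---|
| 5 | 0.397 | 2.17 | 2.2 | 4.13 |
| 10 | 1.587 | 5.50 | 5.5 | 4.13 |
| 20 | 6.349 | 9.29 | 9.3 | 4.13 |
| 40 | 25.40 | −13.6 | −14.2 | 4.13 |

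The theoretical maximum is log2(126) = 6.98 bits, so two of the four simulated values lie outside the possible range. The small gap at 40 microvolts reflects rounding: a 1% change in c moves that entry by about 0.5 bit (c = 25.65 gives −14.1).

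Over a narrower range, a 10% rise from 10 to 11 microvolts gives c = 121 / 63 = 1.921 and a value of 6.12, against 5.50: an 11% increase with the spectrum unchanged. From 20 to 22 microvolts, c = 484 / 63 = 7.683 and the value falls from 9.29 to 9.13. Even the direction of the amplitude effect is not constant.

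**Illustration 2.** A separate simulation: 120 s at 125 Hz, Welch PSD with 250-sample segments, zero-frequency bin dropped, 125 bins; spectra and amplitudes assumed. The identity matched every run.
- Shape fixed (1/f¹), SD 5, 10 and 20 microvolts: c = 0.229, 0.915, 3.659; as-written value 1.764, 5.226, 13.587; proper SE 5.584 throughout.
- Amplitude fixed (SD 10), shapes 1/f⁰, 1/f¹, 1/f²: as-written value 10.025, 5.226, 0.170; proper SE 6.959, 5.584, 2.214.
- Units, for one 1/f¹ signal at SD 10 microvolts: 4.83 when expressed in microvolts, 3.8 × 10⁻¹¹ in volts.
- Amplitude varied by 20% either way and spectral exponent from 0.5 to 1.5: the as-written value correlated 0.33 with log amplitude and −0.92 with the exponent; proper SE correlated 0.00 and −0.99.

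**The case against.** The strongest objection is that this is a slip of wording. The sentence states its aim, a probability density, and the next step names ordinary Shannon entropy; both imply values that sum to 1. The article condenses a fuller specification, and the code is not shown. This stands as far as it goes: division by total power may well have been intended. But the article states a rule, the rule does not do what the same sentence claims for it, and nothing elsewhere settles which will be coded. The rule would also do little harm if every window were first scaled to constant power, because c would then be fixed. The article mentions no such step.

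A reader might infer that SE as defined measures amplitude instead of complexity. The documents and the working do not support that. H(p) remains in the formula, and over the assumed grid the value followed spectral shape far more closely than amplitude. How far power dominates depends on how much power and shape vary between sessions, which the article does not report. For the same reason the 5 to 40 microvolt range, a 64-fold range of power, demonstrates the lack of invariance and is not an estimate of any effect in this trial.

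Two further limits apply. Section 3.3.3 has a data acquisition test before recording, and section 3.3.2 plans independent component analysis for artefacts. Both may reduce spurious power differences, though neither restores scale invariance. The article also gives no ground for supposing that amplifier gain differs between sessions.

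**Conclusion.** The normalising rule in section 3.3.2 is wrong as written. That conclusion rests on algebra alone. SE so defined is not scale-invariant and combines EEG power and measurement units with spectral complexity, so a session difference in it cannot be interpreted as a difference in complexity. The sizes shown (about 2 to 9 bits and then about −14, against a constant 4.13) depend on the assumed spectrum, bins and amplitudes.

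The reach is limited. SE is one of several candidate physiological variables, Higuchi's fractal dimension is planned as another EEG complexity measure, and the sample size in section 4.1 does not depend on SE. It does not follow that the trial's SE results will be invalid: that depends on whether the code follows the sentence or its stated aim. Correction is warranted in either case.

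**What to change.** Replace the normalising sentence with an explicit definition: p_k = PSD_k / sum of PSD over the bins of a stated frequency band; SE = −sum p_k log2 p_k, optionally divided by log2(number of bins) so that it lies between 0 and 1. Check that the analysis code does this before the sessions are compared.

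The cost is one sentence and at most one line of code, with no statistical downside. The change removes dependence on overall amplitude and units. Artefact that alters the shape of the spectrum will still affect SE and must be handled by the planned artefact removal.

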## 1. Introduction

Physical activity is recommended at all ages and for both healthy people and people with functional diversity. The World Health Organization recommends it and even places special emphasis on children and adolescents. In the particular case of people with CP, it is of particular importance. It has demonstrated benefits for motor functions, including enhancing gait speed [1], spasticity [2], balance [3] and muscle strength [4]. It is therefore desirable to find procedures that increase motivation and help to improve the times and routines that this population dedicates to exercise. Detecting the emotional state and fatigue that a subject may have is important, although in this type of population the detection of these states is difficult given individuals’ communication difficulties.

The objective of this experimental protocol is to determine the relationship between physiological measurements and emotional state in children and adults with cerebral palsy (CP). Our research goal is to collect objective and robust information (based on biosignals) about the user’s condition to improve the effectiveness of rehabilitation therapies and the promotion of physical activity, and to determine whether music can improve these outcomes. The knowledge of the user’s emotional state is important to conduct the appropriate activities for their rehabilitation.

The experimentation will be conducted with a group of users belonging to the Association of People with Cerebral Palsy of Seville (ASPACE) and the Director Mercedes Sanroma Special Education School of Seville.

The methodology will be applied to groups of users of different ages with different capacities. For this reason, we have designed a flexible methodology that proposes different tasks according to the context. Certain tasks require physical effort, a factor that must be considered given the potential disruption that it may cause in the data collected [5].

Having an emotional characterization of the user based on their physiological measurements will enable us to obtain a real-time evaluation of the user’s emotions while tasks are being performed. Consequently, activity can be improved by adjusting the required parameters for effective computation, leading to better results.

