It is necessary to resort to more objective methods, and the measurement of biosignals is a good alternative. But in order to rely on biosignals, it is necessary to study whether the changes generated in the biosignals are significant. To determine this, it is necessary to put the subjects in contexts where we can predict and control for what their mood is going to be. These contexts are often activities that are part of their daily routines and for which we have experience of their previous responses. The caregivers and the family environment should support the choice of the routines where the biosignals will be recorded. Whenever possible, these measures can be reinforced with tests to measure emotions and physical state by the subjects themselves or their caregivers, in cases where the subject does not have physical or cognitive abilities to complete them. On the other hand, signal processing should be performed to extract parameters that should then be studied statistically to assess their robustness in determining a state. It is also important to assess how physical movement affects a person’s biosignal data. Appropriate techniques should be studied to eliminate the noise produced by this factor so that it does not affect the extraction of accurate information about the condition. To implement the approach outlined in this paper, two sessions, denoted as sessions 1 and 2, have been devised. Session 1 aims to induce a state of pleasant emotion, while session 2 aims to induce discomfort. These sessions enable us to establish correlations between the parameters derived from the inertial sensors or biosignals being recorded and various emotional states. This process helps identify the most reliable parameters to gauge the users’ states across different contexts objectively. Section 3.3.2 enumerates and elucidates all parameters relevant to the various types of recorded signals. Following the proposed data analysis in Section 4.2, we will select the parameters that most effectively discriminate the physical and emotional states of the subjects.

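### The EEG comparisons have no check on movement, and the statement that the exercising muscles have negligible influence is unsupported, so residual artefact that differs between sessions could be read as an emotional change

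*Protocol article*

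**What the plan says.** Section 3.3.2 of the protocol article lists the EEG variables. Two are complexity measures: "Fractal dimension (FD) of EEG to compute its complexity using Higuchi’s algorithm", and spectral entropy, introduced with "The spectrum entropy (SE) of EEG is a tool to determine the EEG complexity". The third is coherence.

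The paragraph that follows the list makes three statements on muscle activity:
- The muscles doing the exercise are dismissed as a source: "the muscles engaged in the activity are typically distant from the openBCI, and thus their influence is negligible".
- Other sources are acknowledged: "EEG is more likely to be affected by facial muscles, head movements, etc".
- A remedy is planned for those: "For such cases, Independent Component Analysis (ICA) will be utilized".

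Two other sections speak of movement and the signals in general. The Introduction says "Certain tasks require physical effort, a factor that must be considered given the potential disruption that it may cause in the data collected". The Conclusions say "It is also important to assess how physical movement affects a person’s biosignal data", and then "Appropriate techniques should be studied to eliminate the noise produced by this factor".

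On the sessions and the analysis:
- Section 3.3.3: the activities of sessions 1 and 2 are agreed with caregivers for each subject. Sessions 3 and 4 are gentle rehabilitation exercise without and with preferred music.
- Section 5: the aim of the music is that subjects put more time and effort into rehabilitation.
- Section 4.2: variables are chosen by a within-subject permutation test of session 1 against session 2, and kept if significant in a majority of subjects. Sessions 3 and 4 are then compared by Kruskal–Wallis and permutation tests. Average kinetic energy is tested as one more outcome. It is not used to adjust or check the EEG results.
- Section 3.3.2: one of the four inertial units is worn on the head.

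**The concern.** The negligible-influence sentence is a positive claim with no figure, threshold or reference. It settles for the EEG a question that the Conclusions leave open for biosignals as a whole.

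The premise is that the working muscles are far from the headset. That may fit pedalling or limb extension in sessions 3 and 4. It is least secure in sessions 1 and 2, where the activity is whatever is pleasant or uncomfortable for that person, and these are the sessions from which the variables are selected. Sessions 3 and 4 are exposed in another way: if music works as intended, the subject moves more in session 4.

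Fractal dimension and spectral entropy respond to small amounts of added broadband power. If artefact remaining after cleaning differs between two compared sessions, the permutation test will find a difference, and nothing in Section 4.2 would show whether it came from movement. A variable selected on that basis would then be used to judge the effect of music.

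**Working it through.** **Plan's own figure.** The article gives none on this point: no artefact level, no filter band, no expected EEG difference. What follows illustrates the mechanism and does not reproduce anything in the plan.

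**Inputs from the article.** EEG sampling rate 125 Hz with 16 channels (Section 3.3.2); main activity up to 15 min (3.3.3); permutation test of the difference in window means, lowest significance level 0.05 (4.2).

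**Assumptions, none from the article.** EEG with a 1/f^1.5 spectrum; no true emotional effect; artefact in one session only; artefact variance a share *r* of EEG variance, so signal = EEG + √r × artefact with both parts scaled to unit variance.

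**Formulas.**
- Higuchi fractal dimension (FD): slope of log L(k) on log(1/k), k = 1 to 8, with L(k) the mean curve length at lag k.
- Spectral entropy (SE): −Σ p log p / log(number of bins), with p the power spectrum over 1–45 Hz scaled to sum to 1.
- Permutation p-value: (c + 1)/(B + 1), with B = 500 and c the number of permuted differences at least as large as the observed one.

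**Step 1: shift in the mean.** 30 s windows, high-frequency artefact, no filter before FD:

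| Artefact share | FD | SE |
|---|---|---|
| 0% | 1.64 | 0.65 |
| 2% | 1.78 | 0.69 |
| 5% | 1.87 | 0.75 |
| 10% | 1.94 | 0.80 |

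The window SD was 0.01 to 0.04 for FD and 0.02 to 0.04 for SE. At 5%, the shifts are 1.87 − 1.64 = 0.23 for FD and 0.75 − 0.65 = 0.10 for SE.

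**Step 2: how far this depends on filtering.** FD at a 5% share, with background power below 0.5 Hz removed:

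| Filter before FD | Clean | 5% artefact | Shift |
|---|---|---|---|
| none | 1.65 | 1.74 | 0.09 |
| 1–45 Hz | 1.58 | 1.64 | 0.06 |
| 1–30 Hz | 1.47 | 1.49 | 0.02 |

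A further run put the ends of the range at 0.03 (1–30 Hz) and 0.24 (unfiltered), roughly 2 to 20 clean-window SDs. The direction is stable. The size varies about tenfold with processing choices that the article does not state.

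**Step 3: what the permutation test would report.** 15 min / 10 s = 90 windows per session, treated as independent; FD unfiltered; 40 simulated subjects per row. Share of subjects with p < 0.05:

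| Artefact in one session | FD | SE |
|---|---|---|
| none | 3% | 8% |
| 20–60 Hz, 1% | 88% | 10% |
| 20–60 Hz, 2% | 100% | 30% |
| 20–60 Hz, 5% | 100% | 85% |
| 0.5–3 Hz, 5% | 20% | 33% |
| 0.5–3 Hz, 10% | 43% | 83% |
| 0.5–3 Hz, 20% | 98% | 100% |

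The selection rule asks for significance in a majority of subjects. Under these assumptions FD passes it at 1% muscle-band artefact and SE passes it by 5%; with slow movement artefact, SE passes by 10% and FD by 20%. A filter before FD would lower the FD column. Coherence was not simulated.

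**The case against.** The strongest reply is that Section 3.3.2 is more careful than one sentence taken alone suggests, and much of it stands.

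- A reader might infer that the protocol calls all muscle influence on the EEG negligible. It does not. The claim covers only the muscles doing the activity, and facial muscles and head movement are named as the likelier sources, with ICA planned for them.
- A reader might infer that ICA is triggered by visible artefact and so applied more in one session than in another. The text gives no trigger and no rule by session. The phrase "For such cases, Independent Component Analysis (ICA) will be utilized" can equally mean one procedure for those sources wherever they occur.
- A reader might infer a flat contradiction with the Introduction and Conclusions. Those sections speak of possible disruption across all signals, and ICA is itself a noise-removal technique. This is a tension that needs reconciling.
- A reader might infer that the head inertial unit is excluded from EEG processing. The article only says that it is worn.
- Component rejection, filter settings and the fitting of ICA are details that an article may leave to a fuller document. Their absence is no finding.
- The artefact share is assumed, ICA is not modelled, and the size falls sharply with filtering.

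What the reply does not answer is the analysis that Section 4.2 does state. It selects EEG variables on a difference between activities not matched on movement, then applies them where music is meant to change effort, and offers no way to tell movement from emotion.

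**Conclusion.** The concern holds in this limited form. The negligible-influence claim is unsupported and sits uneasily with Sections 1 and 5. The session 1 against 2 and session 3 against 4 comparisons, and the selection rule built on the first of them, include no check that a significant EEG variable reflects more than movement.

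The possible size runs from modest to large: an FD shift of about 0.03 to 0.24 at a 5% muscle share present in one session only, under a 1/f^1.5 background and depending on filtering, with 0.02 under one set of choices. The residue after ICA is not given and cannot be derived. The article therefore does not support saying that FD, SE or coherence will follow movement instead of emotion, only that the planned analysis could not show it if they did.

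**What to change.** 1. Qualify or remove the negligible-influence sentence in Section 3.3.2, and reconcile it with the statements on effort and movement in Sections 1 and 5.
2. State that one identical artefact-removal procedure is applied to every recording in all four sessions.
3. Flag windows with high head motion from the head inertial unit, using one threshold common to all sessions.
4. Repeat the session 1 against 2 and session 3 against 4 comparisons of FD, SE and coherence on the retained windows. Treat an EEG variable as an emotion marker only if its difference persists.

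The head unit detects head motion but not facial-muscle activity, so protection against facial artefact still rests on ICA. This is why item 2 matters as much as item 3.

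The cost is extra processing and some discarded windows. No new sensor or visit is needed.
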